### Randomization

The randomization procedure (1:1 assignment intervention sequence) was determined using a computer random-number generator and was conducted by the Statistics Department at Lille University Hospital (Lille, France) by a person not associated with the study. The two interventions studied are intubation using PVC conical-cuffed tracheal tubes (TaperGuardR, Covidien, Astlone, Ireland) and intubation using PVC standard (barrel)-cuffed tracheal tubes (Hi-LoR, Covidien, Astlone, Ireland). When reintubation is required, a tracheal tube with the same cuff shape as the one used for the first intubation is used.

### Definitions

Abundant microaspiration is defined by significant pepsin level (>200 ng/ml) in >30 % of tracheal aspirates during the 48 h following inclusion. This cut-off was calculated based on the results of previous studies [13, 14].

Microaspiration of oropharyngeal secretions is defined by the presence of alpha-amylase at significant level (1800 UI/l) [28, 29] in tracheal aspirates. Tracheobronchial colonization is defined by positive endotracheal sample without clinical and radiological signs of VAP.

VAP is defined as the presence of radiological and clinical signs consisting of a new and persistent infiltrate on the chest radiograph associated with two of the three following criteria: purulent tracheal aspirates, hyperthermia >38 °C or hypothermia <36 °C and peripheral leucocytosis >10,000/μl or <1,500/μl. A microbiological confirmation is required using tracheal aspirate ≥10^5^ CFU/ml or bronchoalveolar lavage ≥10^4^ CFU/ml [30]. Patients with only clinical and radiological signs without microbiological confirmation are considered to have a suspected VAP. Other ICU-acquired infections are defined elsewhere [31].

Ventilator-associated events (VAE) are defined as a sustained increase in ventilator support (minimum PEP increase >2.5 cm H_2_O, or minimum FiO_2_ increase >15 %) after >2 days of stable or decrease settings [32]. Patients with PEP >75 cm H_2_O or FiO_2_ > 70 % during the first 3 days of mechanical ventilation are tested for these VAC only if a higher stabilization is observed (PEP <5 cm H_2_O, FiO_2_ < 40 % during >2 days).

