### Care standardization

Cuff pressure is checked with a manual manometer every 8 h and kept around 25 cm H_2_O. Patients are ventilated in a semi-recumbent position. Female and male patients are intubated with tracheal tubes sized 7.5 and 8 mm; respectively. Elevation of the head of the bed is checked every 3 h. Oropharyngeal decontamination is performed with 0.10 % chlorhexidine every 3 h. Mechanical ventilation is performed with a positive end-expiratory pressure of at least 5 cm H_2_O, except when contraindicated. Weaning for mechanical ventilation is checked every day to reduce the duration of tracheal intubation. Systematic stress ulcer prophylaxis is not routinely recommended. The shortest duration of sedation is recommended, using a nurse-driven protocol. Tracheal suctioning is performed using an open system. Subglottic secretion drainage is not used, and the respiratory circuit is not routinely changed in study patients.

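### Two thresholds in the VAE rule for severely ill patients do not work: a PEP trigger above 75 cm H2O, and a stabilisation limit below the trial's own PEEP floor

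*Protocol article*

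**What the plan says.** All the figures are in the protocol article.

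- **General rule (Definitions).** A VAE is a sustained rise in ventilator support, "minimum PEP increase >2.5 cm H_2_O, or minimum FiO_2_ increase >15" %, after more than 2 days of stable or decreasing settings.
- **Trigger for the stricter rule (Definitions).** It applies to "Patients with PEP >75 cm H_2_O or FiO_2_ > 70 % during the first 3 days" of mechanical ventilation.
- **Consequence (Definitions).** These patients "are tested for these VAC only if a higher stabilization is observed", which the article specifies as "PEP <5 cm H_2_O, FiO_2_ < 40 % during >2 days".
- **Care standard (Care standardization).** "Mechanical ventilation is performed with a positive end-expiratory pressure of at least 5 cm H_2_O, except when contraindicated".
- **Use (Secondary endpoints).** The proportion of patients with VAE is one of nine listed secondary endpoints.

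PEP is not spelled out. In context it is the PEEP of the care and data-collection sections, and it is read so here.

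**The concern.** The stricter rule decides which of the most severely ill patients can be assessed for VAE at all. Both of its pressure figures look unworkable, and they act in opposite directions. A trigger that no patient reaches lets patients with severe early PEP bypass the rule meant for them. A stabilisation limit that protocol-compliant ventilation cannot meet may shut patients with high early FiO2 out of assessment.

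The observed VAE proportion would then depend partly on how someone chose to interpret the rule. The trial is open-label, investigators follow patients for VAE, and the Blinding section provides blinded confirmation for VAP only. An unworkable written rule therefore leaves room for unblinded choices about what counts.

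**Working it through.** The plan gives no computed figure to reproduce here. The check sets the thresholds side by side and counts the ventilator settings that satisfy each condition.

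**1. The trigger on the article's own scale**

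- Against the PEEP floor: 75 / 5 = 15 times.
- Against the PEP rise that defines an event: 75 / 2.5 = 30 times.
- Against the cuff pressure to be maintained (about 25 cm H2O, Care standardization): 75 / 25 = 3 times.

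The article gives no upper limit for PEEP. Assuming a practical maximum of 20, 25 or 30 cm H2O, the number of settings with PEP above 75 is 0 in each case. The stricter rule is then entered only through FiO2 above 70 %. A patient with high early PEP and FiO2 at or below 70 % is not flagged, and is tested under the general rule.

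**2. The stabilisation limit against the care floor**

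Stabilisation requires PEP < 5; the care standard requires PEEP ≥ 5 unless contraindicated. The two ranges have no common value: even a patient held at exactly 5 fails the condition.

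**3. How much depends on the comma**

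The two stabilisation limits are joined by a comma, with neither *and* nor *or*. The count below uses PEP from 5 cm H2O to the assumed maximum in steps of 0.5, and FiO2 from 21 to 100 % in steps of 1. FiO2 below 40 % gives 19 values (21 to 39).

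| Assumed maximum PEEP (cm H2O) | PEP values ≥ 5 | Flagged by PEP > 75 | Stabilised, comma = AND | Stabilised, comma = OR |
|---|---|---|---|---|
| 20 | 31 | 0 | 0 | 31 × 19 = 589 |
| 25 | 41 | 0 | 0 | 41 × 19 = 779 |
| 30 | 51 | 0 | 0 | 51 × 19 = 969 |

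These are counts of possible settings, not of patients. Under AND, no setting that respects the care floor satisfies stabilisation. Under OR, every qualifying setting qualifies through FiO2 below 40 %, and the PEP limit contributes nothing within the care standard. AND is the likelier reading, because the same paragraph writes *or* in the event definition and in the trigger, where alternatives are meant.

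**The case against.** Several points on the other side are fair.

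- **The 75 may be a misprint, and the full protocol may carry the right figure.** That is possible. A fault in text extraction is not shown, and the decimal in 2.5 survives in the sentence before. Since the article gives no PEEP ceiling, calling 75 unreachable is a judgement of plausibility, though a safe one. The conflict between below 5 and at least 5 does not depend on it.
- **The comma could mean OR.** Then a patient flagged by FiO2 can become testable through FiO2 alone. This stands, and it makes the exclusion conditional. It does not rescue the PEP limit.
- **The floor has an exception.** Patients in whom PEEP is contraindicated could meet a limit below 5. This also stands.

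A reader might also infer more than the article supports:

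- *That both figures prevent severe patients from being counted.* The 75 does the reverse: patients severe by PEP alone stay under the general rule and are tested.
- *That flagged patients are VAE-negative by definition.* The article says when they are tested. It does not say whether an untested patient counts as event-free or as not evaluable.
- *That a known number of patients is lost.* If 10 to 30 % had early FiO2 above 70 %, that would be 312 × 0.10 = 31 to 312 × 0.30 = 94 patients. The article gives no such percentage. The sum also presupposes AND, and some of these patients would never have had the period of stable settings that any VAE requires.
- *That a spurious difference between arms follows.* The same rule applies in both arms, and every ICU uses both cuffs in the crossover. No direction of bias is evident.

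**Conclusion.** The point holds as an error in a stated endpoint rule. The PEP trigger leaves its arm of the rule practically empty, and the stabilisation limit contradicts the trial's care standard. With AND and no contraindication, a patient flagged by FiO2 and ventilated per protocol cannot become testable for VAE. With OR, such a patient can, but only through FiO2.

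The expected harm is missed or misclassified events and poor reproducibility in the sickest patients, for one of nine secondary endpoints. The number affected cannot be derived from the article. The conclusion assumes that PEP means PEEP and that no patient is ventilated at a PEEP near 75 cm H2O.

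**What to change.** Before VAE is derived and the database is locked:

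1. Check the 75 cm H2O trigger against the source cited for the VAE definition, and correct it if it is a misprint.
2. Reconcile the PEP stabilisation limit under Definitions with the PEEP floor under Care standardization. Do this within the endpoint definition and leave the care instruction unchanged.
3. State whether the PEP and FiO2 stabilisation limits are joined by AND or OR.
4. Apply the one corrected rule to all patients, including those already enrolled, as far as the collected data allow.

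No threshold is proposed here; the values must come from the cited definition and the sponsor.

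Correcting the text costs little: enrolment was still open (201 of 312 included by March 2015), and the detailed analysis plan was still to be finalised before lock. The cost of re-derivation is less certain. Data collections lists mean PEEP and highest FiO2 for the first 48 h, and then unspecified VAE data to day 28 or ICU discharge. If the case report form holds daily settings, re-derivation is a programming task. If it holds only a yes/no VAE entry, the rule may not be fully applicable in retrospect, and the report should say so.

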### Study protocol

Inclusions are performed 24 h/24 h, every weekday. After inclusion, tracheal aspirates are collected for 48 h to measure pepsin and amylase. When informed consent is obtained <12 h after intubation, tracheal aspirates collection is started at least 12 h after intubation (Fig. 4). All tracheal aspirates are stored at -20 °C in each hospital’s laboratory, and subsequently sent to the central laboratory at the Lille University Hospital, where all measurements of pepsin and amylase are blindly performed. Quantitative measurement of pepsin is performed by an ELISA technique, and salivary amylase activity is calculated by the difference between total and pancreatic amylase activity. The volume required to perform this analysis is 1 to 2 ml in each tracheal aspirate.

**Fig. 4 Fig4:**
[figure not shown]
Timing of tracheal aspirate collection for pepsin and alpha-amylase measurements

To diagnose tracheobronchial colonization, quantitative tracheal aspirate is performed after intubation, and two times a week. In patients with suspected VAP, quantitative tracheal aspirate or bronchoalveolar lavage is performed to confirm the diagnosis. The choice between tracheal aspirate culture or bronchoalveolar lavage is left to the investigator’s discretion, based on routine practice in each ICU. Investigators prospectively follow patients to detect clinical, radiological or microbiological signs of suspected VAP or VAE. Patients will be followed until ICU discharge or day 28, whichever happens first.

### Care standardization

Cuff pressure is checked with a manual manometer every 8 h and kept around 25 cm H_2_O. Patients are ventilated in a semi-recumbent position. Female and male patients are intubated with tracheal tubes sized 7.5 and 8 mm; respectively. Elevation of the head of the bed is checked every 3 h. Oropharyngeal decontamination is performed with 0.10 % chlorhexidine every 3 h. Mechanical ventilation is performed with a positive end-expiratory pressure of at least 5 cm H_2_O, except when contraindicated. Weaning for mechanical ventilation is checked every day to reduce the duration of tracheal intubation. Systematic stress ulcer prophylaxis is not routinely recommended. The shortest duration of sedation is recommended, using a nurse-driven protocol. Tracheal suctioning is performed using an open system. Subglottic secretion drainage is not used, and the respiratory circuit is not routinely changed in study patients.

### Data collections

At the time of inclusion, the following baseline characteristics are recorded: age, sex, height, body weight, date of hospital admission, date of ICU admission, patient location before ICU admission (home, hospital for >24 h), date of intubation and mechanical ventilation, preexisting comorbidities (diabetes and COPD, chronic restrictive respiratory failure, chronic heart failure, cirrhosis Child B or C, chronic renal failure, esogastroduodenal reflux, immunosuppression), McCabe score, Simplified Acute Physiology Score II, SOFA score, and reason for the ICU admission.

At the time of randomization, the following characteristics are recorded: SOFA score, duration of enteral feeding before randomization, nasal or oral position of the tracheal tube, cuff shape, and tube size.

During the 48 h following randomization, the variables listed below are recorded: ventilatory mode, mean PEEP, mean airway pressure, mean peak pressure, mean cuff pressure, highest FiO_2_, nitric monoxide use, aerosols, vasopressor support, enteral feeding volume, gastric residual volume, stress ulcer prophylaxis, use of prokinetic agents, vomiting, sedation, neuromuscular blockers, Glasgow Coma Score, mean head of bed elevation, prone position, patient mobilization (on chair), patient mobilization outside ICU room, accidental extubation, reintubation, and death.

Until day 28 or until ICU discharge, the following variables are being collected: sedation, transfusion, tracheotomy, extubation failure, accidental extubation, reintubation, shock, transport outside the ICU, mean head of bed elevation, use of proton pump inhibitors, ICU-acquired infection other than VAP (bacteremia, ventilator-associated tracheobronchitis, intravascular catheter-related infection, urinary tract infection, soft tissue infection, and others), duration of antibiotic treatment, duration of mechanical ventilation, length of ICU stay, death, data related to VAE, pepsin and alpha-amylase levels, VAP, and tracheobronchial colonization (Table 1).

**Table 1 Tab1:** Study flowchart follow-up

	Inclusion	H12 to H72	Until Day 28 or ICU discharge	Suspected VAP
Eligibility : check inclusion and exclusion criteria	X			
Randomization	X			
Quantitative TA culture	X		two times a week	X
Pepsin and amylase measurement in all TA for 48 h		X		
Clinical and radiological signs of VAP			X	
Quantitative TA culture or BAL				X
Clinical data			X	

*ICU* intensive care unit; *TA* tracheal aspirate; *VAP* ventilator-associated pneumonia; *BAL* bronchoalveolar lavage

### Blinding

Blinding of physicians, nurses and patients is not feasible in this study. However, pepsin and amylase measurements are performed blindly. VAP diagnosis will be confirmed by at least two independent blinded physicians.

### Trial conduct and data monitoring

Before the start of patient enrollment, all physicians and health-care workers received briefing on the study protocol and data collection in the electronic case report form (eCRF). All documents required for this study are available in each ICU in a folder dedicated to the study. Physicians and/or a clinical research assistant are in charge of daily patient screening and inclusion. The principal investigator is available to all healthcare workers to answer all questions regarding the proper conduct of the study.

### Study outcomes

#### Primary endpoint

The primary endpoint is the proportion of patients with abundant microaspiration of gastric contents. This endpoint will be measured during the 48 h following inclusion in the study.

#### Secondary endpoints

The secondary endpoints include the following:Proportion of tracheal aspirates positive for alpha-amylase per patientProportion of patients with tracheobronchial colonization, and bacterial concentration per patientProportion of patients with VAPProportion of patients with VAEProportion of patients with at least one ICU-acquired infectionAntimicrobial-free daysInvasive mechanical ventilation-free daysLength of ICU stayProportion of patients who die in the ICU

The proportion of tracheal aspirates positive for alpha-amylase per patient will be measured during the 48 h following inclusion in the study. Other secondary endpoints will be measured from inclusion through day 28 or to final extubation if it happens before day 28.

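### One extubation cut-off is set for all secondary endpoints except alpha-amylase; it contradicts the stated follow-up and does not fit ICU stay, ICU death, ICU-acquired infection or the free-day endpoints

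*Protocol article*

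**What the plan says.** The Secondary endpoints section of the protocol article lists nine endpoints. It gives one of them a window of its own: "The proportion of tracheal aspirates positive for alpha-amylase per patient will be measured during the 48 h following inclusion in the study". All the rest share a single rule: "Other secondary endpoints will be measured from inclusion through day 28 or to final extubation if it happens before day 28". That rule therefore covers tracheobronchial colonization, VAP, VAE, ICU-acquired infection, antimicrobial-free days, invasive ventilation-free days, length of ICU stay and death in the ICU.

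Three other places give a different end of observation:

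- Study protocol (text after Fig. 4): "Patients will be followed until ICU discharge or day 28, whichever happens first".
- Data collections: "Until day 28 or until ICU discharge, the following variables are being collected". The list that follows includes "duration of antibiotic treatment, duration of mechanical ventilation, length of ICU stay, death", and also infections other than VAP.
- Table 1, column heading: "Until Day 28 or ICU discharge".

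Nothing in the article restricts the extubation cut-off to the endpoints that depend on a tube being in place.

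**The concern.** The two windows differ for every patient who is extubated for good before day 28 and then stays in the ICU. An extubation cut-off makes sense for events tied to the tube or to tracheal sampling. It makes no sense for an endpoint that is defined by ICU discharge (length of stay), that can occur after extubation (ICU death, bacteremia, catheter or urinary infection), or that mostly accrues after extubation (ventilation-free days).

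This is a stated rule that conflicts with other stated rules, so it is not simply detail left to the statistical analysis plan. An analyst who follows the endpoint section carries the truncation into the results. One who follows the follow-up section departs from the published endpoint definition. If the choice is still open when outcome data are available, two published windows exist for the same mortality, infection and length-of-stay endpoints.

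**Working it through.** The plan gives no figure to reproduce here. The check is a comparison of windows followed by a worked patient.

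**Step 1. Endpoints under the blanket rule.** Nine are listed and alpha-amylase is exempt: 9 − 1 = 8. Three of these (colonization, VAP, VAE) fit an extubation cut-off: 8 − 3 = 5 that do not.

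**Step 2. Effect on each of the five, for a patient finally extubated before day 28.**

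| Endpoint | Window closing at final extubation | Window closing at ICU discharge or day 28 |
|---|---|---|
| Length of ICU stay | equals time to final extubation | observed, censored at day 28 |
| Death in the ICU | deaths after extubation not counted | counted to day 28 |
| ICU-acquired infection | infections after extubation not counted | counted to day 28 |
| Ventilation-free days | only gaps before a reintubation | days from extubation to ICU discharge |
| Antimicrobial-free days | cannot exceed time to final extubation | cannot exceed time to ICU discharge |

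**Step 3. Worked patient.** The timings are assumptions, counted from inclusion: final extubation E = 6, ICU discharge alive D = 12, no reintubation.

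- ICU stay: E = 6 days under the extubation rule; D = 12 days under the follow-up rule.
- Ventilation-free days, extubation rule: 6 − 6 = 0.
- Ventilation-free days, counted to ICU discharge: D − E = 12 − 6 = 6.
- Ventilation-free days, assumed 28-day horizon: 28 − E = 28 − 6 = 22.

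**Step 4. Does ICU discharge work as the end point for free-days?** Take a second assumed patient with the same E = 6 but D = 8. Counted to ICU discharge, this patient has 8 − 6 = 2 ventilation-free days against 6 for the first, although both had the same ventilation and this one left sooner. On a common 28-day horizon both have 22. Aligning with the follow-up section therefore repairs ICU stay, ICU death and infection, but it does not by itself give usable free-days. The same dependence on length of stay would affect antimicrobial-free days.

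**Step 5. Possible size for ICU death.** The article gives neither ICU mortality nor the share of deaths after extubation, so both are assumed. With true ICU mortality m and a share s of those deaths after final extubation, the observed proportion is m × (1 − s).

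- m = 20 %: 0.20 × 0.95 = 19 % with s = 5 %; 0.20 × 0.80 = 16 % with s = 20 %.
- m = 40 %: 0.40 × 0.95 = 38 % with s = 5 %; 0.40 × 0.80 = 32 % with s = 20 %.

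Over this assumed range the undercount is 1 to 8 percentage points.

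**The case against.** The strongest reply is that this is a loosely worded summary sentence. Data collections lists ventilation duration, ICU stay and death as separate variables running past extubation, so the investigators evidently do not intend ICU stay to mean ventilation time, and a detailed analysis plan is promised before database lock. This stands as far as it goes: the data exist, and the remedy for most endpoints is a sentence. It does not remove the contradiction, because the endpoint section states a rule and that rule is wrong for these endpoints.

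It can also be argued that closing infection surveillance when tube exposure ends is defensible. That holds for VAP and VAE. It is weak for an endpoint counting any ICU-acquired infection, since the infections collected include bacteremia and catheter-related, urinary and soft tissue infection, none of which needs a tube.

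Several stronger readings are tempting and not supported:

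- A reader might infer that information between extubation and ICU discharge is lost. The Data collections section says otherwise.
- A reader might take 22 against 0 ventilation-free days as the gap between the article's own sections. It is not: no section states a 28-day horizon for free-days. The article's two windows give 6 against 0 for the worked patient. The zero also rests on the literal reading, since the date of final extubation is the input from which ventilation-free days are usually derived.
- A reader might infer that all ICU deaths are missed. Patients who die while still intubated are counted under either window, up to day 28.
- A reader might infer bias between arms, because the window closes on a post-randomization event in an open-label trial. That would require cuff shape or unblinded care to change time to extubation, which the article does not show.

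**Conclusion.** The contradiction is real. One extubation cut-off is applied to eight of nine secondary endpoints. It is reasonable for three and unsuitable for five, and it conflicts with the follow-up stated in Study protocol, Data collections and Table 1. For patients extubated before day 28 it truncates ICU stay, omits later ICU deaths and infections, nearly abolishes ventilation-free days and bounds antimicrobial-free days by ventilation time. The sizes shown rest on assumed patient timings and assumed mortality; the article supplies neither.

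The consequence is limited to secondary endpoints. The primary endpoint is measured over 48 h and the sample size is built on it, so both are untouched. This should be fixed before database lock, but it does not threaten the trial's main comparison.

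**What to change.** Before database lock, replace the blanket sentence with a window for each endpoint and make it agree with Study protocol, Data collections and Table 1:

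- **VAP, VAE, tracheobronchial colonization and bacterial concentration:** keep inclusion to final extubation or day 28, whichever is earlier.
- **ICU-acquired infection, ICU death, length of ICU stay:** inclusion to ICU discharge or day 28, whichever is earlier, with ICU stay censored at day 28 for patients still in the unit.
- **Ventilation-free and antimicrobial-free days:** count beyond extubation on one fixed horizon, the same for every patient. State as an assumption how days after ICU discharge are treated. Ventilation, antibiotic use and vital status after discharge are not collected, so any rule for death up to a day-28 horizon can use only deaths observed in the ICU unless further data are obtained. Antimicrobial-free days should not be limited to ICU days, because the count would then depend on length of stay.

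For ICU-acquired infection, ICU death and ICU stay, the cost is a wording change using data already collected to ICU discharge or day 28. For free-days it is the same wording change plus the stated assumption. No change to recruitment, the primary analysis or the sample size is needed.
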